##### Cognitive function

2.6.2.5

The selective reminding test (SRT) measures memory from both long-term storage and consistent long-term storage. The test is conducted and scored according to the original instructions [98]. After 20 min, interspersed by other tests, participants are asked to recall the word list, where the number of words recalled correctly constitutes the delayed recall score. To diminish potential learning effects participants will receive different SRT forms in a randomized order at each testing timepoint.

The symbol digit modalities test (SDMT) is a measure of cognitive processing speed and attention using the translation geo-metric symbol numbers from 1 to 9. The number of correct translations by the participant in 90 s is the score [99]. A change of 4 points or more on the SDMT is considered a clinically relevant change [100]. To get a proxy measure of cognitive fatigability number of correct translations are compared for the first 30 s and last 30 s [101].

##### Physical activity

2.6.2.6

Physical activity levels in pwMS are lower than in matched HC [102,103]. Physical activity is in the present study objectively measured using an accelerometer (Axivity AX3, Axivity, Newcastle, UK) worn for seven consecutive days. The accelerometer is placed on the mid-anterior thigh of the weaker leg using self-adhesive tape (Fixomull Stretch, BSN Medical, Hamburg, Germany). Data is sampled at 100 Hz with a sensitivity of ±8G. The setup of the accelerometers and the downloading of raw data are done using OmGuiV.1.0.0.43 (Newcastle University, UK). Thigh-worn accelerometers provide more reliable and valid measurements of physical activity compared to other placements. Data analysis is performed using custom-built software (Propero by [name], Odense, Denmark) as previously described [104]. Additionally, minutes of sedentary, light intensity, moderate intensity, and vigorous intensity physical activities will be determined based on relevant cut-off levels of counts per minute.

### Patient-reported outcomes

2.13

The MS impact scale (MSIS) consists of 29 items assessing the impact of MS on the life of a pwMS from the perspective of the patient. The impact of MS is divided into a physical and a psychological component [105,106]. MSIS score ranges from 29 to 145 points (high scores indicating a larger impact of MS), and a change of 7 points is considered clinically relevant [107].

The MS walking scale (MSWS) assesses the impact of MS on walking abilities and mobility in pwMS via a 12-items questionnaire, where each item is scored from 1 to 5 [108]. The MSWS score is transformed to a percentage score (0–100) of the maximum possible score (a higher score indicating larger impact of MS on walking abilities), and a change of 10.7 points is considered clinically relevant [74].

The modified fatigue impact scale (MFIS) assesses the subjective perception of fatigue impact, which is among the most frequent and disabling symptoms of MS [109]. The MFIS questionnaire score ranges from 0 to 84, with higher scores indicating greater fatigue impact. A score of ≥38 points indicates clinical fatigue [110], and a change of 4 points is considered clinically relevant [111]. The Danish version of MFIS has been validated and shows good reliability [112].

The hospital anxiety and depression scale (HADS) measures emotional distress via 14 items with seven items probing anxiety and seven items probing depression. Each item is scored from 0 to 3 with higher scores representing more emotional distress [113]. HADS was developed for use in medically ill patients and has later been validated in pwMS [114].

The euro quality of life 5-dimension (EQ-5D) is a non-disease-specific questionnaire used to determine quality of life [115,116]. The EQ-5D has previously been used in MS populations [117].

The falls efficacy scale-international (FES-I) is a questionnaire assessing concern of falling when performing different activities and is validated in pwMS [118]. It consists of 16 items which are rated from 1 to 4, where a higher score indicates a greater concern of failing [119]. Additionally, a 12-months falls recall (number of falls, injurious falls) are carried out [120].

The Pittsburgh sleep quality index (PSQI) assesses the subjective sleep quality in a 19-item questionnaire. The total score (global PSQI score) is the sum of all components (range: 0–21): a score ≥5 represents poor sleepers; <5 represents participants with normal sleep quality [121,122].

The Brief Pain Inventory (BPI) measures the level of self-reported pain. The short form of the BPI is used, which consists of 9 items concerning different aspects of pain rated from 0 to 10 [123,124].

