**Methods:**

The presented ‘Power Training in Older MS patients (PoTOMS)’ trial is a national, multi-center, parallel-group, randomized controlled trial. The trial compares 24 weeks of usual care(n = 30) to 24 weeks of usual care and power training (n = 30). The primary outcome is whole brain atrophy rate. The secondary outcomes include changes in brain micro and macro structures, neuromuscular function, physical function, cognitive function, bone health, and patient-reported outcomes.

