### Study design

2.1

The PoTOMS trial is a 24-week national, multi-center, parallel group, randomized controlled trial (RCT) with 24-weeks of follow-up. The present study compares an intervention group of older pwMS receiving 24 weeks of high-load progressive power training (PPT) to a control group of older pwMS receiving usual care, comprising standard healthcare provided to pwMS within the Danish healthcare system. The study design of the PoTOMS trial is depicted in Fig. 1. This study protocol conforms to the SPIRIT statement, and the trial is registered at www.clinicaltrials.gov (registration number NCT04762342).

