### Sample size

2.3

The present study is powered based on the primary outcome; percentage total brain volume change after 24 weeks of PRE in pwMS quantified by structural image evaluation, using normalization, of atrophy (SIENA) [41] and the assumption that PPT is ∼15% more effective than traditional of PRE [49,54]. A two-sample two-sided power calculation showed that a total of 30 subjects are needed in each group to adequately power the study (α = 0.05; power = 0.8; control mean = 0.3204 (SD 0.5253); exercise mean = −0.0148 (SD 0.2698); dropout rate = 16%).

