### Random allocation procedure

2.4

Randomisation to either the PPT group or the control group will be performed after baseline testing by the project coordinator in a 1:1 allocation ratio. Allocation is done by the sealed envelope principle.

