### Outcomes

2.6

All outcomes will be assessed at week 0, 24, and 48. An overview of outcomes can be seen in Table 3.

**Table 3 tbl3:** Overview of test.

	Pre intervention test	Post intervention test	Follow-up test
Brain MRI			
MP2RAGE	x	x	x
T2 Space, dark fluid	x	x	x
DKI	x	x	x
Leg MRI			
Leg 2D Dixon	x	x	x
Muscle strength			
Bilateral leg press	x	x	x
Hand grip	x	x	x
Knee extension	x	x	x
Knee flexion	x	x	x
Plantar ankle flexion	x	x	x
Dorsal ankle flexion	x	x	x
Neural function			
ITT	x	x	x
EMG	x	x	x
Cognition			
SRT	x	x	x
SDMT	x	x	x
Clinical disability			
EDSS	x		
Physical function			
T25FWT	x	x	x
SSST	x	x	x
6MWT	x	x	x
9SSA	x	x	x
NHPT	x	x	x
1STS	x	x	x
5STS	x	x	x
Standing balance	x	x	x
Blood sample			
Neurodegenerative factors	x	x	x
Neurotrophic factors	x	x	x
Immunological factors	x	x	x
Bone metabolism	x	x	x
Body composition			
DXA	x	x	x
Physical activity			
Accelerometry	x	x	x
Questionnaires			
MSIS	x	x	x
MSWS	x	x	x
HADS	x	x	x
MFIS	x	x	x
EQ5D	x	x	x
FES-I	x	x	x
PSQI	x	x	x
ADL	x	x	x
BPI	x	x	x

Abbreviations: MP2RAGE: Magnetization Prepared 2 Rapid Acquisition Gradient Echo, DKI: Diffusion kurtosis imaging, T25FWT: Timed 25-foot walk test, SSST: Six spot step test, 6MWT: Six-minute walk test, 9SSA: Nine step stair accent, NHPT: Nine-hole peg test, 1STS: one time sit-to-stand test, 5STS: five time sit-to-stand test, SRT: Selective reminding test, SDMT: Symbol digit modality test, EDSS: Expanded disability status scale, DXA: Dual-energy X-ray absorptiometry MSIS: Multiple sclerosis impact scale, MSWS: Multiple sclerosis walking scale, MFIS: Modified fatigue impact scale, HADS: Hospital anxiety and depression scale, EQ-5D: Euro quality of life 5-dimension, FES-I: Falls efficacy scale-international, PSQI: Pittsburgh sleep quality index, ADL: Activities of daily living, BPI: Brief pain inventory.

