### Statistics

2.8

Characterization of the study sample across groups will be carried out using multiple baseline demographic and anthropometric variables (reported as number of observations, mean ± SD or median ± IQR, and proportions were appropriate). Data is checked for normality via visual inspection of histograms and quantile-quantile plots. In case of non-normality, appropriate data transformations will be performed. To investigate the effect of the 24 weeks PPT intervention and the 24 weeks follow-up period on the primary outcome (i.e., whole brain atrophy rate), a linear mixed model with repeated measures is used with group and time as fixed effects and participant id as random effects. The secondary outcomes will be analyzed analogous to the primary outcome. The analyses are performed following the intention-to-treat principle (i.e., all participant data are included, but without use of “last observation carried forward”) as the mixed model allows for missing value. In addition, a per-protocol analysis is performed based on adherence levels (only including participants that attend ≥80% of the planned PPT training sessions). An alpha level of 0.05 is used for all comparisons.

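### If the 12-month falls recall is repeated at each visit, 54% of the week-24 window precedes randomisation and the falls rate ratio is attenuated

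*Protocol article*

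**What the plan says.** Under Patient-reported outcomes (section 2.13), directly after the falls efficacy scale (FES-I), the protocol article adds that "a 12-months falls recall (number of falls, injurious falls) are carried out". The Outcomes section (2.6) says "All outcomes will be assessed at week 0, 24, and 48". Table 3 marks FES-I at all three visits but has no row for the falls recall.

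Allocation "will be performed after baseline testing by the project coordinator in a 1:1 allocation ratio" (section 2.4), so week 0 precedes randomisation. The Study design section (2.1) describes 24 weeks of training in a "randomized controlled trial (RCT) with 24-weeks of follow-up".

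The abstract lists among the secondary outcomes "neuromuscular function, physical function, cognitive function, bone health, and patient-reported outcomes". The Statistics section (2.8) adds: "The secondary outcomes will be analyzed analogous to the primary outcome". For the primary outcome that means a linear mixed model with group and time as fixed effects and participant as random effect, meant to examine both the training and the follow-up period. No shorter recall period, falls diary or restriction to falls since the last visit is given.

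**The concern.** Visits are 24 weeks apart, but the recall reaches back about 52 weeks. A count taken at week 24 would therefore include falls that happened before anyone was allocated to training. On average those falls do not differ between arms, so they pull a ratio or percentage comparison towards no difference. Successive windows also overlap, so the same fall can be reported at two visits.

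At stake is what the falls comparison can answer. The trial wants to describe a training period and a follow-up period separately, and a 12-month total aligns with neither. A small difference at week 24 could be taken as evidence that training does little for falls when much of the shrinkage comes from the window. The recall period is fixed when the data are collected; unless fall dates are recorded, no later analysis can recover the timing from a 12-month total.

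**Working it through.** **Inputs.** Recall window: 12 months, taken as 52 weeks (section 2.13). Visits: weeks 0, 24 and 48 (section 2.6). Randomisation: after week-0 testing (section 2.4). Training: weeks 0 to 24; follow-up: weeks 24 to 48 (section 2.1). The documents give no fall rate and no expected effect on falls, so both are assumed below.

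**The plan's own figure.** The only sample-size figure is 30 per group for brain atrophy (section 2.3). With a difference of 0.3204 + 0.0148 = 0.3352 and SDs of 0.5253 and 0.2698, n = (1.960 + 0.842)² × (0.5253² + 0.2698²) / 0.3352² = 24.4, rounded up to 25. Allowing for 16% dropout, 25 / 0.84 = 29.8, so 30. The figure reproduces and does not depend on the falls recall.

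**Composition of each window.**

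| Visit | Before randomisation | Training | Follow-up |
|---|---|---|---|
| Week 0 | 52 of 52 weeks | 0 | 0 |
| Week 24 | 52 − 24 = 28 (53.8%) | 24 (46.2%) | 0 |
| Week 48 | 52 − 48 = 4 (7.7%) | 24 (46.2%) | 24 (46.2%) |

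Taking a year as 365.25 days changes the week-24 share only to 54.0%.

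**Overlap.** The week-0 and week-24 windows share 28 weeks, as do the week-24 and week-48 windows. The week-0 and week-48 windows share 4.

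**Effect on the rate ratio.** Assume a constant fall rate in the control arm and before randomisation, and a rate ratio RR during training.

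- Week 24: observed ratio = (28 + 24 × RR) / 52.
- Week 48, effect confined to training: (4 + 24 × RR + 24) / 52, which is the same expression.
- Week 48, effect persisting through follow-up: (4 + 48 × RR) / 52.

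| Assumed RR | Week 24 | Week 48, training only | Week 48, persisting |
|---|---|---|---|
| 0.50 | 0.77 | 0.77 | 0.54 |
| 0.60 | 0.82 | 0.82 | 0.63 |
| 0.70 | 0.86 | 0.86 | 0.72 |
| 0.80 | 0.91 | 0.91 | 0.82 |

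At week 24, log(observed) / log(RR) runs from 0.38 at RR 0.50 to 0.43 at RR 0.80, so roughly 40% of the effect remains on the log scale.

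**Effect on the absolute difference.** With λ falls per week, the expected difference between arms in the week-24 count is (28 + 24)λ − (28 + 24 × RR)λ = 24λ(1 − RR). A 24-week recall gives the same expected difference. What changes is the noise, because each count also carries 28 weeks that training could not have affected.

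**With recall since the previous visit.** The share before randomisation falls to 0% at both later visits, and the week-24 ratio equals RR.

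**The case against.** The strongest objection is that repetition is inferred. The falls sentence names no visit, Table 3 has no falls row, and falls appear in neither the aims nor the statistics section. The statement that all outcomes are measured three times is not literally universal, since Table 3 gives EDSS at baseline only. A baseline fall history used to describe the sample would fit the text. This stands as a possibility, but it is the less natural reading: the recall is attached to FES-I, which is marked at all three visits, and the one baseline-only item is shown as such.

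A reader might go further and infer that a real reduction in falls would be hidden, or that the falls comparison is invalid. The documents do not support that. The shared pre-randomisation weeks favour neither arm; they shrink a ratio at week 24 but leave the expected difference in counts intact. At week 48, 92% of the window follows randomisation, and an effect that lasts through follow-up would show almost in full.

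A reader might also infer that counting a fall at two visits biases the group contrast. Overlap mainly adds correlation within participants, which the participant random effect absorbs at least in part. It does not bias the contrast at a given visit beyond the dilution shown above.

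Nor is it a finding that the article names no count model for falls. That choice is commonly left to the analysis plan, which is not shown.

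Timing also matters. The article is dated February 2024 and expects the study to finish in mid-2024. If that refers to the last week-48 visits, the last week-24 visits fell around January 2024, and a changed form would reach few participants.

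**Conclusion.** The point holds as a modest and conditional one. If the 12-month recall is repeated at each visit, 54% of the week-24 window precedes randomisation. The week-24 rate ratio is then attenuated (0.50 to 0.77, 0.70 to 0.86) and the absolute difference becomes noisier. The week-48 window cannot separate training from follow-up: it shows 0.77 or 0.86 if the effect ends with training, and 0.54 or 0.72 if it persists.

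The window shares follow directly from the stated visits and recall period. The sizes rest on a constant fall rate, accurate recall and assumed rate ratios. Falls are a minor item among the patient-reported outcomes.

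**What to change.** Keep the 12-month recall at week 0 as baseline fall history. At weeks 24 and 48, ask for falls and injurious falls since the previous test visit, and add a falls row to Table 3.

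For visits already completed under 12-month recall, flag the window in the data and the report, and do not interpret the week-24 count as a training-period outcome. Describe the week-48 count as covering training and follow-up together, with 4 weeks before randomisation.

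If the recall was intended for baseline only, state that in section 2.13 and do not analyse it as an outcome.

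The cost is one changed question on the form and a sentence or two of text. The real downside is that changing it mid-trial leaves two recall windows in the same data set. Counts from the two are not directly comparable, so the window used must be recorded for each visit. If nearly all visits are done, flagging and restrained interpretation are what remain.

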### Data handling

2.7

All digital data, except questionnaires, will be visually inspected for quality at the time of collection and stored in accordance with the rules defined by the Danish Data Protection Agency. All analogue data will undergo double data entry and will be stored in accordance with the rules defined by the Danish Data Protection Agency both in analogue and digital form. All data will be entered pseudonymized and the decryption key will be stored separately from the data. Access to data is provided by Aarhus University.

### Statistics

2.8

Characterization of the study sample across groups will be carried out using multiple baseline demographic and anthropometric variables (reported as number of observations, mean ± SD or median ± IQR, and proportions were appropriate). Data is checked for normality via visual inspection of histograms and quantile-quantile plots. In case of non-normality, appropriate data transformations will be performed. To investigate the effect of the 24 weeks PPT intervention and the 24 weeks follow-up period on the primary outcome (i.e., whole brain atrophy rate), a linear mixed model with repeated measures is used with group and time as fixed effects and participant id as random effects. The secondary outcomes will be analyzed analogous to the primary outcome. The analyses are performed following the intention-to-treat principle (i.e., all participant data are included, but without use of “last observation carried forward”) as the mixed model allows for missing value. In addition, a per-protocol analysis is performed based on adherence levels (only including participants that attend ≥80% of the planned PPT training sessions). An alpha level of 0.05 is used for all comparisons.

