Progressive resistance exercise (PRE) has resulted in improved physical and neuromuscular function in young and middle-aged pwMS [36,37], with dynamic muscle strength as well as rate of force development (RFD) being particularly susceptible towards adaptation [21]. Of note, such adaptations are predominantly attributed to functional adaptations of the CNS, with improved neural drive [[38], [39], [40]]. In addition, data from a pilot randomized controlled crossover study involving n = 35 pwMS suggests that 24 weeks of PRE improves cortical thickness and reported a trend towards reduced whole brain atrophy [41]. Despite these positive effects of PRE in pwMS, it has not yet been investigated in older pwMS; however, data from older healthy individuals show that PRE induces positive effects on both physical function [42,43] and neuromuscular function [42,44]. This is mainly achieved through increased neural drive to the muscles [42,45] as well as muscle hypertrophy [46,47]. The former is suggestive of an improved CNS ability to recruit and fire motor neurons following PRE.

PRE can be performed as progressive power training (PPT; PRE performed with moderate-to-high loading at maximal concentric movement velocity) hereby increasing demands of the CNS to activate the muscle. PPT induces comparable improvements in muscle strength as traditional PRE, but greater improvements in muscle power [48,49]. This is important, as pwMS have substantial muscle strength reductions during fast concentric contractions [21] and since muscle power, more so than muscle force, is a strong predictor of physical function in older adults [50,51]; nevertheless, power training has only been sparsely investigated in pwMS so far [52], and still not in older pwMS where it may have the most profound effects.

Consequently, the primary aim of the present study is to compare the effects of 24 weeks of power training to a “usual care” control group on neurodegeneration (i.e., annualized whole brain atrophy rate) in older pwMS (≥60 years). A secondary aim is to evaluate the effects of 24 weeks power training on additional macro and micro brain structures, neuromuscular function, physical function, cognitive function, bone health and patient-reported outcomes.

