For the primary aim, we test the hypothesis that older pwMS performing 24 weeks of power training will elicit a reduced annualized whole brain atrophy rate compared with the control group. For the secondary aim we test the hypothesis that performing 24 weeks of power training will improve brain micro and macro structures, neuromuscular, physical, cognitive function, bone health, and patient-reported outcomes.

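### The mixed model lists group and time but no group-by-time term or week-24 contrast, so its group coefficient is a time average and not, in general, the 24-week training effect

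*Protocol article*

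**What the plan says.** The Statistics section (2.8) gives the purpose of the primary model as "To investigate the effect of the 24 weeks PPT intervention and the 24 weeks follow-up period on the primary outcome". It then lists the terms: "a linear mixed model with repeated measures is used with group and time as fixed effects and participant id as random effects". It adds: "The secondary outcomes will be analyzed analogous to the primary outcome". The article names no interaction, no contrast and no primary time point for the model.

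The question itself is stated elsewhere. In the Introduction, "the primary aim of the present study is to compare the effects of 24 weeks of power training to a “usual care” control group", and the hypothesis is that "older pwMS performing 24 weeks of power training will elicit a reduced annualized whole brain atrophy rate compared with the control group". The Sample size section (2.3) is based on "percentage total brain volume change after 24 weeks of PRE in pwMS". The Outcomes section (2.6) says: "All outcomes will be assessed at week 0, 24, and 48". The Primary outcome section (2.6.1) gives the same three times for MRI, and no power training is described for the second 24 weeks.

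**The concern.** A model with group and time as its only fixed effects has one parameter that separates the arms: a group difference taken to be the same at every time level. The trial asks about the difference produced by the first 24 weeks.

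The two agree only if the effect really is constant over the modelled time levels, or if those levels happen to be chosen so that the average equals the 24-week effect. For an outcome measured as a level at baseline and later, constancy cannot hold, because randomisation makes the expected difference zero at week 0.

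The treatment effect on every level-type secondary outcome (strength, walking, cognition, questionnaires) would then be understated. The primary estimate could be diluted by a period without training.

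**Working it through.** **1. The plan's own figure.** Inputs from Sample size (2.3): means 0.3204 and −0.0148, so the difference is 0.3352; SDs 0.5253 and 0.2698; two-sided α 0.05; power 0.80; dropout 16%.

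- n = (1.960 + 0.842)² × (0.5253² + 0.2698²) / 0.3352² = 7.849 × 0.3487 / 0.1124 ≈ 24.4, so 25 per arm.
- 25 / 0.84 = 29.8, so 30 per arm. The stated size reproduces.
- With 25 analysed per arm, SE = √(0.3487 / 25) = 0.118. Power for the 0–24 week difference is 81% by normal approximation and 79% by an unequal-variance t-test.

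Annualising multiplies the means and SDs by the same constant, so power is unchanged.

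**2. What the group coefficient estimates.** In balanced data with a participant random intercept, it equals the difference between arms in participant means over the time levels.

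**3. Level-type secondary outcomes (weeks 0, 24, 48).** Let r be the share of the week-24 effect retained at week 48 (an assumption; the article gives none). The expected coefficient is (0 + 1 + r)/3 of the week-24 effect: 33% at r = 0, 50% at r = 0.5 and 67% at r = 1. A chance baseline difference b that persists at all three visits enters in full, since (b + b + b)/3 = b. A change-from-baseline contrast removes it.

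As an illustration, assume a 0.5 SD effect, 25 per arm and equal correlation ρ between visits. The SE in SD units is √[(2/25)(1 + 2ρ)/3] for the main effect and √[(2/25) × 2(1 − ρ)] for the week-24 change contrast.

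| ρ (assumed) | SE, main effect | z, r = 0 to 1 | Power | SE, change | z | Power |
|---|---|---|---|---|---|---|
| 0.8 | 0.263 | 0.63 to 1.27 | 9–24% | 0.179 | 2.80 | 80% |
| 0.5 | 0.231 | 0.72 to 1.44 | 11–30% | 0.283 | 1.77 | 42% |

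**4. Primary SIENA outcome, intervals 0–24 and 24–48.** Let f be the share of the effect that persists in the follow-up interval (an assumption). The expected coefficient is (1 + f)/2 × 0.3352, with SE = 0.118 × √((1 + ρ)/2). Power is by normal approximation.

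| f | Coefficient | Share of 24-week effect | Power, ρ = 0 | Power, ρ = 0.8 |
|---|---|---|---|---|
| 0 | 0.168 | 50% | 52% | 32% |
| 0.5 | 0.251 | 75% | 85% | 61% |
| 1 | 0.335 | 100% | 98% | 85% |

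Simulated t-tests on participant means gave 51% for the first cell. A mixed-model simulation with 2,000 per arm gave additive coefficients of 0.163, 0.242 and 0.333 for f = 0, 0.5 and 1. The interaction model gave 0.336, 0.329 and 0.331 for the 0–24 effect.

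**5. Other choices of time level, with f = 0 and ρ = 0.**

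- Annualised rates over 0–24 and 0–48: the participant mean is ¾ of the first interval plus ¼ of the second. The coefficient is 75% of the effect; SE = 0.118 × √0.625 = 0.093; power 77%.
- Cumulative change from baseline at 24 and 48: the mean is the first interval plus ½ of the second. The coefficient is 100% of the effect; SE = 0.118 × √1.25 = 0.132; power 72%.
- Only 0–24 modelled: no dilution.

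**The case against.** The strongest reply is that the sentence may be shorthand. It never says that the interaction is excluded, and the article condenses a fuller document that is not shown. Its stated purpose, to look at the intervention and the follow-up periods, cannot be met by an additive model, so an interaction may well be intended. That is fair, and the article does not show that the investigators decided against one. But it did not leave the model to another document. It lists the fixed and random effects, and the term that carries the treatment effect is missing from the list.

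The reply is also right about the primary outcome, where a reader might infer more than the article supports:

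- *That the primary effect is always halved.* The article does not say which SIENA intervals form the time levels. The 50% figure needs separate 0–24 and 24–48 intervals and a benefit confined to training.
- *That the planned power is lost whenever the benefit fades.* This is false. With uncorrelated intervals, 80% power holds down to about 40% persistence: (1 + f)/2 must reach 2.80 × 0.0835 / 0.3352 = 0.70, where 0.0835 is the SE at ρ = 0. With full persistence, the additive test is the more powerful one.
- *That two primary tests at 0.05 give a family-wise error of 9.75%.* A model with a single group parameter yields one group test. The figure also assumes independent tests, and the two intervals share the week-24 scan.

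The aim and the sizing do make the 24-week question identifiable. The model just does not target it. None of these replies helps the level-type secondary outcomes, where even full retention leaves the coefficient at two-thirds of the effect.

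**Conclusion.** The concern stands in a conditional form. As written, the model's only between-arm parameter is an average over time levels, while the aim, hypothesis and sample size concern the effect after 24 weeks.

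The defect is firmest for level-type secondary outcomes. There the coefficient recovers one-third to two-thirds of the week-24 effect in balanced data, for retention between none and full, and it absorbs chance baseline imbalance.

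For the primary outcome, the coefficient matches the sized-for effect only under some interval choices or if the effect persists equally. The loss ranges from none to half of the effect when little or nothing persists. Persistence and correlation are assumptions. The article gives neither, so the power figures show a range and are not predictions.

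**What to change.** Replace the model sentence with one that states:

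- Fixed effects: group, time (categorical) and group × time, with participant as random effect. State which SIENA intervals form the time levels.
- Primary test: the between-arm difference in annualised SIENA change over weeks 0–24, as a single two-sided test at 0.05. If the SIENA intervals are the time levels, this is the group difference at the 0–24 level.
- Follow-up contrasts (24–48 or 0–48): secondary.
- Secondary outcomes: the between-arm difference in change from baseline to week 24, which for level-type outcomes is the week-24 group-by-time term.

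The cost is one sentence, settled before outcomes are compared by arm. No new data are needed. The sample size stays at 30 per group, because the 0–24 contrast is the one it was calculated for.
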